### Intervention

In the experimental condition, the complete multidisciplinary teams (all registered nurses, psychologists, physicians, and psychiatrists) will be trained in the application of the guideline via the TtT-e program. By training complete multidisciplinary teams, including all team members, irrespective of full- or part-time staff, we aim for 100% coverage. In the TtT-e program, three types of actors are involved: masters, trainers, and trainees. The training is applied on two levels: first, trainers are trained by masters. Subsequently trainees are trained by trainers. The training program is supported by two e-learning modules. The first module is developed for trainees. It consists of video vignettes in which experienced nurses, psychologists, and psychiatrists interact with suicidal patients (played by actors). The total running time of this module for trainees is 60 minutes. In addition to the e-learning module for trainees, a second e-learning module was developed specifically for trainers. It provides a video of the first training session provided by masters to trainers, which was processed into an e-learning format allowing trainers to review the training session.

The TtT-e is a 1-day small interactive group program supported by e-learning modules, which reflects the PGSB recommendations
[1]. The PGSB recommendations served as the starting point to set the content of the TtT-e program within the PITSTOP suicide study. First, all guideline recommendations were listed and clustered into six themes: 1) basic clinical skills when discussing suicidality; 2) systematic assessment of suicidal behavior; 3) diagnosis of the current suicidal condition; 4) safety and continuity of care, including participation of the patient’s relatives; 5) treatment of suicidal behavior; and 6) chronic suicidal conditions. Second, clusters were transformed into six modules and scheduled according to the sequence of action in common clinical practice. For each module, goals and competences were set in terms of professional behavior. Furthermore, the PGSB recommends systematic investigation of the suicidal condition of patients by using the Chronological Assessment of Suicidal Events (CASE) interview
[32]. Based on its outcome, risk and protection factors for suicide of individual patients are weighted. Subsequently, structured diagnosis, treatment strategy, and a safety protocol are determined. In the TtT-e program, the CASE interview is the overall framework for each of four role plays in which one trainee acts as a suicidal patient and the other trainee interviews the ‘patient’ via the CASE interview.

In the control condition, no additional actions next to IAU will be undertaken.

To survey adherence to the training program by trainers, graduate students will randomly visit training sessions, and will rate adherence on a four-point Likert scale: 1, very strong adherence, to 4, very low adherence.

### Sample size

For the primary outcome (suicide ideation) we calculated the effect size according to the recommendations of Twisk
[33]. The number of patients that needed to be included was set to 423. This number is sufficient to find a small effect size (Cohen’s *d*) of 0.3, assuming an alpha of 0.05 and statistical power of 1-beta = 0.80. A correction of 20% for clustering of effects within departments is applied. An average number of 20 patients per department will be included.

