### Recruitment

Recruitment of MHIs took place during meetings and conferences on suicide prevention in The Netherlands between 2008 and 2010. MHIs were invited to participate in the study. When MHIs expressed willingness to participate, they were requested to indicate at least two multidisciplinary departments for adult care to be included in the study. To prevent exchange of training materials between the experimental and control condition, MHIs were explicitly asked to provide departments that were based in separate buildings and/or on separate locations, and to be sure that staff members were not exchanged or shared between departments. This resulted in 43 participating departments distributed over 10 MHIs (Figure 
1). Various types of mental health care departments are represented in the study (inpatient and outpatient care, crisis departments, and long-stay departments) treating patients of various diagnostic categories (personality disorder, depressive disorder, anxiety disorder, and psychotic disorder) and of various ages.

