1 demonstrates that the included departments are located in urban and rural regions of The Netherlands. We conclude that the included departments provide a representative sample of all departments in mental health care institutions in The Netherlands. We will compare the patient characteristics of the sample with the national patient population available via the Dutch Association of Mental Health and Addiction Care (GGZ Nederland, Amersfoort, The Netherlands), and will describe the results to check external validity.

A possible limitation of the study is that budget cuts, reorganizations, and layoffs, commonplace in Dutch mental health care, may interfere with the study aims. Attrition of patients to the study is a further challenge, since not all patients will complete the ROM at all intervals due to the lack of time of professionals or inexperience with the ROM
[37]. Using a strict protocol and local research assistants/nurses, we aim for limited drop-out. To prevent drop-out, research assistants will help patients to complete the questionnaires and will make appointments for follow-up assessment.

Commitment of both management and employees of the participating MHIs is crucial. To date, willingness of both management and employees to apply the TtT-e program is excellent. The findings from the current study may be generalized to implementation of other (mental) health care guidelines.

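### The 423 patients, 20 per department and 43 departments in the sample size plan do not fit together, and 423 supports 80% power only with a low ICC and complete follow-up

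*Protocol article*

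**What the plan says.** The Sample size section of the protocol article states: "The number of patients that needed to be included was set to 423". This is said to be enough to "find a small effect size (Cohen’s *d*) of 0.3", "assuming an alpha of 0.05 and statistical power of 1-beta = 0.80". It goes on: "A correction of 20% for clustering of effects within departments is applied. An average number of 20 patients per department will be included". No ICC, number of departments or drop-out rate is given there.

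The number of departments is given under Recruitment: "This resulted in 43 participating departments distributed over 10 MHIs". The Discussion repeats 43, and Table 1 lists them with their allocation (21 experimental, 22 control).

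The primary comparison (Statistical analyses) is of changes in BSS score, so it needs the T1 assessment at 3 months or discharge. The Discussion warns: "Attrition of patients to the study is a further challenge". It also describes steps to limit drop-out.

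**The concern.** Three numbers that should determine one another do not. Total patients, patients per department and number of departments are each stated, and the product of the last two is about twice the first. A reader cannot tell whether recruitment ends at 423 or near 860, nor which cluster size the 20% correction assumes.

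This matters because the effect of clustering depends on cluster size. The same 20% allows for a different ICC at 20 per department than at 10. The 423 is also worded as patients included, while the primary analysis depends on patients who reach T1. If the trial stopped at 423 included and lost some at T1, a null result could be read as lack of effect at d = 0.3 when power had been below the 80% stated.

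**Working it through.** **Inputs.** From Sample size: d = 0.3, alpha 0.05, power 0.80, clustering correction 20%, 20 patients per department, total 423. From Recruitment: 43 departments. Sidedness is not stated; two-sided reproduces 423 and one-sided does not (138 per arm gives 276 × 1.20 = 331). The article gives no ICC and no attrition rate, so values used for these are assumptions, apart from the ICC implied by the 20%.

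**Step 1: reproduce 423.** A two-sample t-test at d = 0.3 needs 175.4, so 176 per arm, or 352 in total. Then 352 × 1.20 = 422.4, rounded up to 423. The normal approximation gives 175 per arm: 350 × 1.20 = 420. Dividing by 0.80 instead gives 440 or 437.5, which does not match. So 423 is the individually randomised total times 1.20, with no further factor.

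**Step 2: fit of the three numbers.**
- 43 × 20 = 860
- 423 / 20 = 21.2 departments
- 423 / 43 = 9.8 patients per department

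**Step 3: ICC covered by the 20%.** With design effect DE = 1 + (m − 1) × ICC, setting DE = 1.20 gives ICC = 0.20 / (m − 1).
- m = 20: 0.20 / 19 = 0.0105
- m = 9.84: 0.20 / 8.84 = 0.0226

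**Step 4: power on the plan's own terms.** At DE = 1.20 the effective total is 423 / 1.20 = 352.5. The noncentrality is 0.3 × √(352.5 / 4) = 2.82, and the normal approximation gives Φ(2.82 − 1.96) = 80.4%. With a t reference on (departments − 2) degrees of freedom at ICC 0.0105, power is about 76% for 21 departments of 20 and about 82% for 43 departments of 9.8.

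**Step 5: power beyond those terms.** Effective N = N / DE, with m = N / 43 after any loss, and noncentral t on 41 degrees of freedom. Equal cluster sizes and equal arms are assumed. Pair matching and the institution level are ignored.

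| Patients over 43 departments | ICC 0.0105 | ICC 0.02 | ICC 0.05 | ICC 0.10 |
|---|---|---|---|---|
| 423 analysed | 82% | 79% | 71% | 59% |
| 423 included, 20% missing T1 (338) | 74% | 71% | 64% | 55% |
| 423 included, 25% missing T1 (317) | 71% | 69% | 62% | 53% |
| 860 analysed | 98% | 96% | 87% | 71% |
| 860 included, 25% missing T1 (645) | 93% | 91% | 81% | 67% |

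Example, second row at ICC 0.02: m = 338 / 43 = 7.86; DE = 1 + 6.86 × 0.02 = 1.137; effective N = 338 / 1.137 = 297; noncentrality = 0.3 × √(297 / 4) = 2.59; power 71%.

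**The case against.** A reader might infer that 423 simply fails to deliver 80% power. The article does not support that. On its own inputs 423 reproduces exactly and gives 80.4% by the normal approximation. The 76% in step 4 belongs to a trial of 21 departments, whereas 43 are randomised; over 43 the figure at the same ICC is 82%. The larger shortfalls all rest on ICC or attrition values that the article does not contain.

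Nor must the two totals contradict each other. One is worded as a number needed and the other as an average that will be reached, so 423 may be a minimum and 860 a plan with ample margin. At 860, power stays above 80% at ICC 0.05 even with 25% missing T1.

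It is also tempting to call an ICC of 0.01 implausible because Table 1 mixes crisis, inpatient and outpatient departments and several diagnoses. Table 1 says nothing about the variance of change in BSS. Departments that differ in baseline level need not differ in change, and they were matched on diagnosis and treatment duration. Finally, the article condenses a fuller protocol, so the missing ICC is not an error in itself.

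All of this stands. It makes the power shortfall conditional and removes any claim about which ICC is true. It does not supply the link between 423, 20 and 43. If 860 is the plan, the 80% statement does not describe the trial, since power at the implied ICC would be about 98%. If 423 is the plan, 20 per department is wrong by a factor of two. Nor does it provide an attrition margin within 423, because step 1 shows that the clustering correction accounts for the whole inflation.

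**Conclusion.** The point holds as an unreconciled inconsistency in figures the trial relies on, together with a power statement that is conditional but not presented as such. Two parts follow from the article alone: 43 × 20 = 860 against 423, and 423 = 352 × 1.20 with nothing left for missing T1. The 80% for 423 is met with complete follow-up and an ICC up to about 0.011 at 20 per department or about 0.023 at 9.8 (normal approximation; a t reference on 41 degrees of freedom gives 79% at ICC 0.02 over 43 departments).

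Beyond that, the size depends on assumptions. With 20% missing T1, 423 over 43 departments gives about 74% at ICC 0.0105 and 71% at 0.02. With no loss it gives 71% at ICC 0.05 and 59% at 0.10. The documents do not establish that the trial as run would be underpowered: at 860 included it would exceed 80% over much of this range.

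**What to change.** Rewrite the Sample size paragraph on one consistent basis, using all 43 departments, and say whether each total means included or analysed.

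- **Option A.** Give 43 × 20 = 860 included as the planned size and keep 423 as a minimum number analysed. State power over a range of assumed ICC and attrition, for example about 91%, 81% and 67% at ICC 0.02, 0.05 and 0.10 with 25% missing T1.
- **Option B.** Keep 423, correct the average to about 10 per department over 43, and state power as conditional: about 79%, 71% and 59% at ICC 0.02, 0.05 and 0.10 before attrition, and lower after it.

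In either case give the ICC and cluster size behind the 20%, show the design effect formula, and state the expected loss at T1. If the fuller protocol already holds these values, quote them in place of the illustrative ones here.

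The cost is one paragraph. Option A needs no patients beyond the stated 20 per department. Option B needs none either, but replaces the 80% with a less favourable figure. Recruitment was ongoing at the time of the article, so the target should be clarified before recruitment stops.

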#### Statistical analyses

As the study is a design with different levels, all outcomes will be analyzed using multilevel models. Patients are nested within departments (level 1), and departments are nested within MHI centers (level 2). Multilevel models are hierarchal systems that estimate random coefficients and variance components for each level
[33]. Random intercepts will be included in the multilevel models. Data will be analyzed on an intention-to-treat basis.

To examine the hypothesis that suicide ideation in patients of professionals who received the TtT-e program is more likely to be reduced than patients of professionals who did not receive TtT-e, we will compare changes in BSS scores between patients of teams allocated to the intervention with patients of teams in the control group. To examine differences in the number and intensity of suicide attempts, scores on items 20 and 21 of the BSS will be dichotomized (YES/NO, LOW/HIGH) and compared between treatment groups using logistic regression. To examine the effect of the intervention on treatment satisfaction, mean scores of the four satisfaction items between groups will be compared. For the economic evaluation, missing cost and effect data will be imputed using multiple imputation according to the MICE algorithm
[34]. The results of the imputed datasets will be pooled using Rubin’s rules
[35]. Bias-corrected and accelerated bootstrapping with 5,000 replications will be used to estimate 95% confidence intervals around the mean difference in total costs between the treatment groups. Incremental cost-effectiveness ratios (ICERs) will be calculated by dividing the difference in mean total costs between the treatment groups by the difference in mean effects between the treatment groups. Bootstrapping will also be used to estimate the uncertainty surrounding the ICERs, which will be graphically presented on cost-effectiveness planes. Cost-effectiveness acceptability curves will also be estimated. Cost-effectiveness acceptability curves will show the probability that the intervention is cost-effective in comparison with usual care for a range of different ceiling ratios (that is, the willingness to pay for one extra unit of effect)
[36].

Approval was obtained from the Medical Ethics Committee of the VU University Medical Centre, Amsterdam, The Netherlands (registration number: 2011/151). All local medical ethics committees agreed with this approval.

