## Method

### Design

This is a multicentre cluster randomized controlled trial (RCT) in which multidisciplinary teams from mental health institutions (MHIs) are matched in pairs with respect to patient diagnoses and average treatment duration. Subsequently, pair members are randomly allocated to treatment conditions.

A MHI is a regional organization with a specific catchment area of patients
[24]. For example, in 2011, MHI Rivierduinen had a catchment area of 1.1 million people within an area of approximately 1,500 km^2^ in the region of South Holland. MHI Rivierduinen has 44 psychiatric departments and treats an overall number of 24,753 patients annually with 2,726 employees
[25]. Most of the psychiatric departments are specialized in the treatment of patients of specific diagnostic categories, such as depression or personality disorder.

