### Randomization procedure

Eligible departments were clustered in pairs. It is assumed that similar types of patients treated for a similar duration of time are likely to be comparable. The first criterion for matching departments was the main diagnostic category of patients. For instance, a department that reported that 60% of the patients had a main diagnosis of depression was matched with another department that reported a comparable percentage of depressive patients. Within groups of comparable patient diagnoses, departments were matched with departments with comparable average treatment duration of patients. Members of matched pairs were randomly allocated to either IAU (internet, newsletter, books, publications, and congresses; control) or IAU with the TtT-e program (intervention). Randomization was performed by an independent researcher of the research institution (EMGO + Institute for Health and Care Research, Amsterdam, The Netherlands) who was not involved in the study. Table 
1 displays an overview of the types of departments, patient diagnoses, and results of the matching procedure. Healthcare professionals are aware of the allocation outcome, but patients are not.

**Table 1 T1:** Overview of the mental health institutions (MIHs), departments, main patient diagnoses, and results of the matching procedure

**MHI**	**Department**	**Average treatment duration of patients (days)**	**Main diagnosis**	**Condition**
Delfland	Inpatient	1,532	Depression	EXP
Delfland	Inpatient	1,308	Depression	CON
Delfland	Outpatient	624	Depression	EXP
Dimence	Outpatient	600	Depression	CON
Parnassia	Outpatient	21	Depression	CON
Parnassia	Inpatient	16	Depression	EXP
Delfland	Outpatient	740	Depression	CON
Parnassia	Inpatient	730	Depression	EXP
Pro Persona	Crisis	1	Depr/bord/crisis	CON
Pro Persona	Crisis	1	Depr/bord/crisis	EXP
Parnassia	Inpatient	250	Personality	EXP
Dimence	Inpatient	400	Personality	CON
Dimence	Crisis	1	Depr/bord/crisis	EXP
Parnassia	Crisis	1	Depr/bord/crisis	CON
Friesland	Outpatient	582	Depression	EXP
Friesland	Outpatient	814	Depression	CON
Friesland	Outpatient	743	Depression	EXP
Friesland	Outpatient	602	Depression	CON
Parnassia	Outpatient	90	Depression	EXP
Parnassia	Outpatient	21	Depression	CON
Viersprong	Personality	240	Personality	CON
Eindhoven	Personality	300	Personality	EXP
Eindhoven	Outpatient	150	Depression	CON
Eindhoven	Inpatient	104	Depression	EXP
Rivierduinen	Inpatient	35	Depression	EXP
Rivierduinen	Outpatient	240	Depression	CON

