Parnassia	Outpatient	41	Depression (older adults)	EXP
Parnassia	Outpatient	Missing	Depression (older adults)	CON
Dimence	Inpatient	90	Depression	CON
Pro Persona	Outpatient	365	Depression	EXP
Altrecht	Outpatient	42	Depr/bord/crisis	EXP
Altrecht	Inpatient	150	Depr/bord/crisis	CON
Vincent van Gogh	Outpatient	172	Personality	CON
Vincent van Gogh	Outpatient	54	Personality	EXP
Rivierduinen	Inpatient	270	Personality	CON
Rivierduinen	Outpatient	180	Eating disorder	EXP
Viersprong	Outpatient	244	Personality	EXP
Parnassia	Outpatient	240	Addiction	CON
Rivierduinen	Crisis	Missing	Depr/bord/crisis	EXP
Rivierduinen	Inpatient	Missing	Personality	CON
Vincent van Gogh	Inpatient	96	Mood disorder NOS	CON
Vincent van Gogh	Inpatient	20	Schizophrenia	EXP
Parnassia	Inpatient	371	Depression (older adults)	CON

CON, control; Depr/bord/crisis, Depression/borderline/crisis; EXP, experimental; personality, personality disorder; MIH, mental health institution; missing, missing data; NOS, not otherwise specified.

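### The stated multilevel model omits the matched pair within which departments were randomised, and the 43rd department has no pair; the planned test is valid but may be somewhat conservative

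*Protocol article*

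**What the plan says.** - **Randomisation.** Under Design, departments are "matched in pairs with respect to patient diagnoses and average treatment duration", after which "pair members are randomly allocated to treatment conditions". Randomization procedure repeats this: "Members of matched pairs were randomly allocated to either IAU" or to IAU plus the training. Main diagnosis is the first matching criterion and average treatment duration the second.
- **Number of departments.** Recruitment reports: "This resulted in 43 participating departments distributed over 10 MHIs". Table 1 lists each department with its condition.
- **Analysis model.** Statistical analyses fixes the hierarchy for all outcomes: "Patients are nested within departments (level 1), and departments are nested within MHI centers (level 2"). It adds: "Random intercepts will be included in the multilevel models". Analysis is by intention to treat. The section mentions neither the pair nor a department without a partner.
- **Sample size.** "The number of patients that needed to be included was set to 423", for d = 0.3, alpha 0.05 and power 0.80, with 20% added for clustering within departments.

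**The concern.** Randomisation was restricted within pairs, so the treatment contrast is formed within pairs. If the two members of a pair resemble each other in outcome, the true variance of the contrast is smaller than a model without the pair estimates. Standard errors are then too wide, the test runs below its nominal level, and some of what the matching was meant to gain is not collected. With 43 clusters this could matter.

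This is not a detail left to an analysis plan. The article lists the levels of the model and leaves out the level at which allocation was restricted.

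The second issue is that 43 is odd. A procedure that allocates the two members of a pair cannot by itself assign every department, so at least one department's condition needs a separate explanation.

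**Working it through.** **1. Count of Table 1.** Consecutive rows form pairs of one experimental and one control department.

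- 43 departments: 21 experimental and 22 control, in 10 MHIs.
- 21 pairs use 2 × 21 = 42 departments. 43 − 42 = 1: the last row (control, inpatient, depression in older adults, 371 days) has no partner.
- 14 pairs lie within one MHI and 7 cross two. Four MHIs contain two or three complete pairs each. Pair and MHI are therefore crossed, and neither can replace the other.
- Quality of matching: 4 of 21 pairs differ in listed main diagnosis. Both durations are known in 19 pairs; 6 of these differ three-fold or more, although log duration correlates about 0.91 within pairs overall. Duration is missing for three departments.

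**2. The plan's own sample size.** The two-sided t-test for d = 0.3, alpha 0.05 and power 0.80 needs 176 per arm, or 352. 352 × 1.20 = 422.4, rounded up to 423. The stated figure is reproduced, with no credit for matching.

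**3. The ICC implied by the 20% correction.** 1 + (m − 1) × ICC = 1.20.

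- m = 20 (the stated average): ICC = 0.20/19 = 0.0105.
- m = 423/43 = 9.84: ICC = 0.20/8.84 = 0.0226.

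**4. What pairing could save.** Let f be the share of between-department variance common to a pair (an assumption). The correlation of department means within a pair is r = f × ICC / (ICC + (1 − ICC)/m), and the standard error falls by 1 − √(1 − r). With m = 9.84 and f = 0.5:

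| ICC | r | Fall in standard error |
|---|---|---|
| 0.0105 | 0.00525/0.1111 = 0.047 | 2.4% |
| 0.0226 | 0.0113/0.1219 = 0.093 | 4.8% |
| 0.05 | 0.025/0.1466 = 0.171 | 8.9% |
| 0.10 | 0.05/0.1915 = 0.261 | 14.0% |

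**5. Power against the planned model, on the Table 1 layout.** Department means were simulated with 423 patients, d = 0.3 and f = 0.5, and fitted by REML. The planned model has an MHI intercept.

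(a) Pair intercept in place of MHI, 20 degrees of freedom, 20,000 runs:

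| ICC | Planned model | With pair | Gain (points) | Type I error, planned |
|---|---|---|---|---|
| 0.0105 | 83.4% | 83.7% | 0.3 | 4.8% |
| 0.0226 | 80.3% | 81.5% | 1.2 | 4.6% |
| 0.05 | 74.5% | 77.5% | 3.0 | 3.8% |
| 0.10 | 63.3% | 70.2% | 6.9 | 3.2% |

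(b) Pair intercept crossed with MHI, 4,000 runs:

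- ICC 0.05: power 75% to 79%; type I error of the planned model 4.0%.
- ICC 0.10: power 63% to 72%; type I error of the planned model 2.9%.
- ICC 0.01 to 0.02: gain 1 to 3 points. Part of this reflects a type I error near 6% in the pair model, because no small-sample correction was applied.

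**6. Sensitivity to f.** A simpler comparison of department means, unpaired t-test (21 v 22) against paired t-test (21 pairs), without MHI, 100,000 runs:

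| ICC | f = 0 | f = 0.5 | f = 0.8 |
|---|---|---|---|
| 0.0105 | 82.0% v 79.1% | 82.5% v 80.9% | 83.0% v 82.1% |
| 0.0226 | 78.5% v 75.5% | 79.5% v 79.3% | 80.1% v 81.8% |
| 0.05 | 70.7% v 67.6% | 72.3% v 75.4% | 73.7% v 80.9% |
| 0.10 | 59.2% v 56.0% | 60.6% v 69.1% | 61.8% v 79.0% |

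A strict paired test costs about 3 points if the pairs share nothing, because its degrees of freedom fall from 41 to 20. It gains clearly only when both the ICC and f are substantial.

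**The case against.** **The loss may be nothing.** It depends on an ICC and a within-pair share that the document does not give. At the ICC its own correction implies, the gain is 0 to 3 points. This stands. A reader might infer that the precision from matching is simply lost; the documents do not support that. Nor do they support figures based on 20 patients per department, which need 43 × 20 = 860 patients against the stated 423.

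**MHI absorbs part of the pair effect.** With 14 pairs inside one MHI this is plausible. It does not remove the conservatism: with MHI in the model, type I error is still about 3 to 4% at ICC 0.05 to 0.10.

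**Loose matching means little to gain.** This is fair: the more the pairs differ, the smaller f is. The differences should not be overstated, though. Several pairs mix inpatient and outpatient care, but setting was never a matching criterion, so this is not failed matching.

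**Covariates may be in a fuller plan.** This also stands. Measurement procedure promises control for mode of data collection in the final analysis, which Statistical analyses does not repeat, so that section is not a complete list of terms. It cannot be inferred that imbalance will go unadjusted. The levels of the hierarchy, however, are listed explicitly and the pair is not among them.

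**The 43rd department may have been randomised.** It may. The article does not say otherwise; it only describes a procedure that cannot cover this department. That it lacks random allocation is an inference the text does not support.

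**Conclusion.** The mismatch between design and analysis is certain: allocation is within 21 matched pairs, and the stated model has department and MHI only. No bias or inflated type I error follows from omitting the pair. The planned test is valid, and conservative so far as pairs share outcome variance.

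The size is uncertain. At an ICC of about 0.01 to 0.02 the cost is nil to about 3 power points. With 423 patients and an ICC of 0.05 to 0.10 it is about 3 to 9 points. Both ranges take half of the between-department variance as common to the pair. Neither the ICC nor that share is in the document, so the figures are conditional. The upper ends come from fits with the pair crossed with MHI, and at the low ICCs part of that gain reflects the missing small-sample correction. A low ICC is not assured, as departments range from 1-day crisis units to inpatient care averaging 1,532 days.

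The unexplained allocation of the unpartnered control department depends on no assumption. The change is worth making because it is cheap and aligns the analysis with the randomisation, not because a large loss of power has been shown.

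**What to change.** - Add a random intercept for the matched pair, crossed with MHI, to the multilevel models, with a small-sample degrees-of-freedom correction. A random term suits better than a fixed one: its variance can shrink towards zero if matching achieved little, and the unpartnered department still contributes to the contrast.
- As an option, adjust for the matching variables, main diagnosis and average treatment duration. Say in advance how the three departments without a duration will be handled.
- State how the 43rd department was allocated. Keep it in the intention-to-treat analysis as its own singleton stratum, and add a sensitivity analysis without it. Dropping it from the primary analysis would conflict with the stated intention-to-treat principle.

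The cost is a few sentences, some degrees of freedom and a slightly more complex model. A strict paired analysis would go from 41 to 20 degrees of freedom and lose about 3 power points if pairs share no variance. In the simulations the random pair term did not lower power, though without the correction its test ran near 6%, which is why the correction belongs in the same sentence.

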### Inclusion and exclusion criteria

Departments are considered eligible for participation if they treat patients aged ≥18 years and if professionals consider a need for training in suicide prevention skills, and their management are willing to provide support including financial support for covering loss of production.

Since basic clinical skills, such as establishing a therapeutic alliance with the patient, are an important part of the training and e-learning, it is expected that patients who report no suicide ideation at baseline will benefit from the TtT-e program. Therefore, all patients irrespective of being suicidal at baseline will be included. Since admitted patients will often be affected by emotional and/or cognitive problems, patients who are emotionally and/or cognitively unable to complete questionnaires properly will be excluded. Whether a patient is able to enter the study will be left to the discretion of the staff.

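### The primary contrast is change in BSS with no stated adjustment for the T0 score, which costs precision and leaves the estimate exposed to T0 imbalance

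*Protocol article*

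**What the plan says.** Under Statistical analyses, the article plans multilevel models with random intercepts for all outcomes, with patients in departments and departments in mental health institutions. It states: "Data will be analyzed on an intention-to-treat basis". For the primary hypothesis, "we will compare changes in BSS scores between patients of teams allocated to the intervention with patients of teams in the control group". No baseline covariate is named there. The only adjustment foreseen anywhere is in Measurement procedure, for mode of data collection if differential item functioning shows bias.

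BSS (range 0 to 38) is the primary outcome. Patients are assessed at admission (T0) and at three months or just before an earlier discharge (T1). Under Inclusion and exclusion criteria, "all patients irrespective of being suicidal at baseline will be included", and staff judge whether a patient is able to take part. Randomization procedure says that professionals know the allocation and patients do not.

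On missing data, the article says: "For the economic evaluation, missing cost and effect data will be imputed using multiple imputation according to the MICE algorithm". It gives no method for the primary outcome. The Discussion expects that some patients will not complete every assessment.

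**The concern.** A patient at or near 0 on the BSS at T0 has no room to fall, while a high scorer tends to fall by regression to the mean. Change therefore depends on T0. An arm that happens to hold more suicidal patients will show more apparent recovery, whatever the training does.

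This design makes such imbalance plausible. Patients enter after their department has been allocated, at the discretion of staff who know the allocation. Measurement starts at different moments in the two arms: once all staff are trained, or once the control department hears its allocation. Some matched pairs in Table 1 differ visibly, for example a 35-day inpatient department with a 240-day outpatient one.

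At stake are precision that the T0 measurement could supply at no cost, and an estimate that moves with whatever T0 difference occurs. A second, conditional issue is that a change score cannot be computed without T1.

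**Working it through.** **The plan's own figure.** From Sample size: "The number of patients that needed to be included was set to 423". The same section targets a standardised difference of d = 0.3 at the 5% level (sidedness not stated) with 80% power, and raises the total by 20% for clustering. A two-sided t-test needs 176 per arm, or 352 in total. 352 x 1.2 = 422.4, rounded up to 423. The figure reproduces and contains no allowance for dropout.

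**Change against baseline-adjusted T1.** Let rho be the T0-T1 correlation within arm and set both variances to 1. The documents do not give rho, so it is assumed at 0.3, 0.5 and 0.7. Clustering is ignored in the variance ratio.

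- Variance of change: 2(1 - rho).
- Variance of T1 given T0: 1 - rho^2.
- Ratio, adjusted to change: (1 - rho^2) / [2(1 - rho)] = (1 + rho)/2.
- Extra patients needed by the change score for equal precision: 2/(1 + rho) - 1.
- Shift of the change contrast from a T0 imbalance of 0.15 SD (an assumed size): (1 - rho) x 0.15.
- Power with d = 0.3 in T1 SD units: Phi(0.3 x sqrt(n/(2v)) - 1.96), where v is the variance above and n = 423/1.2/2 = 176.25 per arm.

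| rho | Var, change | Var, adjusted | Ratio | Extra patients | Power, change | Power, adjusted | Shift (SD) |
|---|---|---|---|---|---|---|---|
| 0.3 | 1.40 | 0.91 | 0.65 | 54% | 0.66 | 0.84 | 0.105 |
| 0.5 | 1.00 | 0.75 | 0.75 | 33% | 0.80 | 0.90 | 0.075 |
| 0.7 | 0.60 | 0.51 | 0.85 | 18% | 0.95 | 0.98 | 0.045 |

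At rho 0.5 the shift is 0.075/0.3 = one quarter of the target effect. Under a linear model the T0-adjusted estimate does not carry this shift.

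**Missing T1.** No attrition rate is given, so 10 to 40% is assumed. If 423 patients enter and only those with T1 are analysed, n becomes 423 x (1 - attrition)/2.4 per arm. With d = 0.3 on the analysed scale, power falls from 0.80 to 0.76, 0.71, 0.65 and 0.59 at 10, 20, 30 and 40%.

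For bias, a large simulation took normal scores, no treatment effect and about 28% missing T1, with missingness depending on T0:

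| Missingness depends on T0 | Complete-case change, rho 0.5 | Complete-case change, rho 0.7 | Complete-case T0-adjusted |
|---|---|---|---|
| Equally in both arms | 0.00 SD | 0.00 SD | about 0.00 |
| In the experimental arm only | 0.07 SD | 0.04 SD | about 0.00 |
| In opposite directions | 0.14 SD | 0.08 SD | about 0.00 |

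**The case against.** **The article is a summary.** It gives the primary contrast one clause, and covariates and missing-data handling often sit in a fuller plan that is not shown. The adjustment for mode of data collection appears in Measurement procedure and is not repeated under Statistical analyses, so that section is not a full model specification. This stands against any claim about what will be left out. It does not remove the point, because the contrast that the article does name is change.

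**Comparing changes could mean a group-by-time model.** The list of levels serves all outcomes, including satisfaction, which is measured only at T1, so the absence of an occasion level proves little. That is fair, and such a model would keep patients without T1. With complete data, however, its group-by-time interaction equals the difference in mean change, so the baseline issue remains.

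**Change scores are valid under randomisation.** Agreed: the contrast is unbiased on average, and regression to the mean acts in both arms. Where imbalance comes from selective entry, T0 adjustment handles only the part that T0 explains and is no reliable cure.

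**The sizes are hypothetical.** The values of rho and the 0.15 SD imbalance are assumed. Equal variances are doubtful with many scores near the floor. The article does not say whether d = 0.3 is on the T1 or the change scale. If it is the latter, the change analysis keeps its planned power and the table shows efficiency forgone, not a shortfall.

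**Missing T1 may do little harm.** T1 is brought forward for patients discharged early, and assistants help with questionnaires and follow-up appointments. The simulation shows bias only when missingness depends on T0 differently by arm.

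**Conclusion.** The point holds as a recommendation to change the primary model. As described, the analysis compares changes in BSS with no stated T0 adjustment, although T0 is collected. The cost is 18 to 54% more patients for the same precision at rho 0.7 to 0.3, and a shift of 0.045 to 0.105 SD for each 0.15 SD of T0 imbalance. Both rest on equal variances, assumed correlations and no allowance for clustering. It is an efficiency and conditional-error problem; the trial is not invalid because of it.

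Three stronger readings are not supported:

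- A reader might infer that baseline is deliberately excluded, or that every patient without T1 is dropped. The article says neither. What can be said is conditional: a change score run without imputation is a complete-case analysis, at odds with the intention-to-treat statement in a trial that expects attrition.
- A reader might infer that the trial will report two BSS differences on two patient sets, one imputed and one not. The imputation sentence does not identify the effect data as BSS, and it neither extends imputation to the primary test nor rules it out.
- A reader might infer a biased primary estimate. That would need selective entry or differential loss, which the design makes possible but the documents do not show.

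**What to change.** Make the primary model T1 BSS on arm, adjusted for T0 BSS, within the multilevel structure already stated. Preferably include patients without T1 by extending the planned multiple imputation to the primary outcome, and say so beside the intention-to-treat statement. Keep the change-score comparison as a sensitivity analysis.

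Two additions are not required. A longitudinal model that forces a common T0 mean assumes arms equal at baseline, which is doubtful when unblinded staff judge entry after allocation. A separate estimate in patients with T0 BSS above 0 is optional, since the trial deliberately includes patients without ideation and expects them to benefit.

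The cost is analysis wording only: T0 and T1 BSS are already collected and the imputation method is already planned. With recruitment reported as ongoing, the change should be fixed before outcomes are examined by arm.
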